## Abstract

**Background:**

There are significant gaps in the implementation and uptake of evidence-based guideline recommendations for cardiovascular disease (CVD) and diabetes in Australian general practice. This study protocol describes the methodology for a cluster randomised trial to evaluate the effectiveness of a model that aims to improve the implementation of these guidelines in Australian general practice developed by a collaboration between researchers, non-government organisations, and the profession.

**Methods:**

We hypothesise that the intervention will alter the behaviour of clinicians and patients resulting in improvements of recording of lifestyle and physiological risk factors (by 20%) and increased adherence to guideline recommendations for: the management of CVD and diabetes risk factors (by 20%); and lifestyle and physiological risk factors of patients at risk (by 5%). Thirty-two general practices will be randomised in a 1:1 allocation to receive either the intervention or continue with usual care, after stratification by state. The intervention will be delivered through: small group education; audit of patient records to determine preventive care; and practice facilitation visits adapted to the needs of the practices. Outcome data will be extracted from electronic medical records and patient questionnaires, and qualitative evaluation from provider and patient interviews.

**Discussion:**

We plan to disseminate study findings widely and directly inform implementation strategies by governments, professional bodies, and non-government organisations including the partner organisations.

## Background

Cardiovascular disease (CVD) represents a substantial and increasing portion of healthcare expenditure and practitioner workload
[1]. It is estimated that 9 in 10 adult Australians have at least one risk factor for CVD
[2]. Behavioural risk factors include smoking, nutrition, alcohol, physical activity, and being overweight or obese. The physiological risk factors include high blood pressure and dyslipidaemia
[3].

Primary care providers are well placed to help reduce the incidence of CVD. General practitioners provide clinical services to approximately 88% of Australians each year and are in an ideal position to screen for risk factors and provide brief interventions including advice about behavioural risk factors as well as medications
[1]. However, there are numerous barriers to implementation at the patient, practitioner, practice, and system levels
[4-7].

The Australian Government Department of Health and Ageing, the National Health and Medical Research Council, the National Heart Foundation of Australia, The Royal Australian College of General Practitioners, The Cardiac Society of Australia and New Zealand and the National Vascular Disease Prevention Alliance have published guidelines that address the major behavioural and physiological risk factors for vascular disease. These guidelines synthesise the evidence for preventing CVD and provide clear messages for primary care providers on what targets to aim for and what strategies might be best employed at the patient provider interaction.

A number of these guidelines refer to the 5As framework, which describes how general practice staff can intervene to prevent CVD
[8]. This framework describes the pathway and informs the role of different providers and services in preventive care (Figure
1).

**Figure 1 F1:**

The 5As conceptual model.

The guidelines have been widely disseminated and well received. However implementation requires more than dissemination
[9], it requires a tailored approach to generate change in clinicians behaviour
[10], and there exists evidence of gaps between the guideline recommendations and their implementation in Australian general practice
[7,11,12]. Some of the reasons for the failure to implement prevention guidelines are related to the complexity of guideline recommendations and patient, practitioner, and practice barriers
[7,13], including lack of capacity to provide brief interventions or refer for more intensive education and support
[14,15]. Patients’ understanding of prevention is variable: they lack knowledge about what preventive care is what is relevant to them, and there is a tendency for patients with low health literacy and education attainment to be less likely to ask for, and therefore to receive, preventive care
[16,17]. The culture of individual practices, their openness to change, and the number and experience of providers, all influence the ability to implement preventive guideline recommendations
[18].

The Preventive Evidence into Practice (PEP) study is a partnership between New South Wales, Flinders, Monash, Bond, and Queensland Universities, the Royal Australian College of General Practitioners (RACGP), the National Heart Foundation of Australia (NHFA), and the BUPA Foundation. The PEP study is a national, cluster randomised control trial of an intervention designed to support general practices to implement the recommendations of evidence-based clinical management guidelines for the prevention of CVD in general practice among patients aged 40 to 69 years.

This study aims to evaluate the impact of the PEP intervention on: The behaviour of doctors and nurses in general practice in assessing and recording risk factors and providing interventions to address these; and patient behavioural and physiological risk factors.

We hypothesise that, for patients aged 40 to 69 years, the PEP intervention measured at the practice level over 12 months will improve: by 20% recording of behavioural and physiological risk factors; by 20% the adherence to the recommendations of guidelines for the management of these risk factors; and by 5% the lifestyle and physiological risk factors of patients with the risk factors.

## Methods

### Study design

The study is a cluster randomised controlled trial conducted in general practices in four states. This design was chosen because the primary intervention will be at the practice level and outcomes will be measured at the patient level.

### Randomisation

Practices will be randomly assigned to intervention and late intervention (control) groups after stratification into blocks by state and practice size—i.e., the number of general practictioners (GPs) in a practice—using a computer-generated randomization list. Randomisation will be conducted centrally, after completion of the baseline general practice and practice nurse (PN) surveys, by one of the investigators, a statistician not involved in the data collection or intervention (UJ). Results of the randomisation will communicated to the project management committee prior to the commencement of the intervention.

### Setting

The study is being conducted in general practices in four primary care organisations (Medicare Locals) in urban areas during 2012 and 2013.

### The intervention

#### Intervention development

The process for intervention development broadly followed the framework for design of complex interventions
[19]. In order to inform the development of the PEP intervention we initially conducted a review of the literature
[20]. This identified effective strategies for implementation of guidelines, including establishing small group education sessions with patients, clinician prompts and decision aids, audit and feedback, and external facilitation
[21]. Educational interventions that are interactive, provided feedback to participants, include an objective assessment of education needs and involve small groups are more likely to be effective
[22,23]. Small group interventions are most effective because they combine evidence-based material with peer influence
[24]. Audit and feedback can be effective in providing more preventive care
[25]. The variation of effect can be explained by the different ways in which audits are conducted and how feedback is provided. External facilitation has been shown to be effective in improving preventive care
[26]. Facilitation is usually included as part of a multifaceted intervention that includes auditing medical records.

We then conducted a mixed method study involving eight Sydney based general practices which included qualitative interviews with eight staff from two divisions of general practice, one allied health provider, eight GPs, four PNs, three practice managers and 24 patients. We also conducted a clinical audit of medical records in the eight practices for CVD preventive activities (for 2,409 patients aged 40 to 69 years). The findings from this, and the literature review, were discussed at a workshop involving the investigators and partners and external stakeholders including consumers, professional organisational representatives, and policy makers. The intervention was then piloted in three Sydney general practices and evaluated through audio recording of facilitation visits and interviews with practice staff before and after the intervention. The analysis resulted in changes to the audit feedback to practices, the program of practice visits, and the resources provided to practices. Following the pilot a facilitator manual was developed and discussed among the investigators prior to finalisation.

#### Description of intervention

The intervention is at the practice level. It will be carried out over a six-month period, and consists of a training workshop, three practice visits by a facilitator in each state based in the Medicare Local, and three follow-up phone calls. The facilitators will be trained together using the facilitator manual and case examples from the pilot study.

The training workshop for GPs and PNs in each state on the prevention of CVD will be overseen and presented by a Chief or Associate Investigator, the Intervention Facilitator and a Division of General Practice/Medicare Local staff member. GPs and PNs from each of the intervention practices will attend the workshops. The format of the workshop will include an introductory presentation followed by case studies and role plays using simulated patients. The workshop introduces the 5As for smoking, nutrition, alcohol, physical activity, overweight, blood pressure, cholesterol, diabetes and absolute cardiovascular risk, and kidney disease. Guidelines that provide unambiguous advice and require fewer changes to practice are easier to implement. Thus, guideline recommendations have been synthesised across the 5As framework into a quick reference guide on two sides of an A4 sheet (Figure
2). These will be used as the basis for case discussion in the workshop.

**Figure 2 F2:**
[figure not shown]
Reference guide: summary of guideline recommendations across the 5As.

A clinical audit will be provided to the GPs and PNs at baseline and 12 months for patients aged 40 to 69 without heart or kidney disease, stroke, or diabetes. This will focus on body mass index (BMI) and waist circumference, BP, lipids, fasting glucose, and absolute cardiovascular risk. This will include analysis of both the recording of behavioural and physiological risk factors and the risk factors themselves. Comparative data are provided from other practices together with a commentary prepared by an investigator in each state asking questions and suggesting areas for improvement.

The three practice visits will occur at regular intervals within the six-month intervention period. Each practice will be asked to identify a prevention coordinator who is the key contact person for the research at the practice level (preferably the PN). Each practice visit will be of approximately 1 to 1.5 hours duration and include the GP(s), the PN, and possibly the practice manager. The practice visits will be conducted by the Intervention Facilitator and are designed to occur at regular intervals in order to build momentum and facilitate change at the practice level. They will discuss the provision of preventive care for each of the behavioural and physiological risk factors across the 5As (Figure
3).

**Figure 3 F3:**

The intervention.

Practice visit one will occur between one and four weeks post the training workshop. At this visit, the baseline audit results will be reviewed and two to three goals for improvement established. These goals might be to improve recording of certain risk factors, and intensify prescribing or advice given or referral to other services. Resources and local referral links will be provided and discussed at this initial visit as necessary.

Practice visit two will occur between three and four weeks after visit number one. The purpose of this visit will be to reflect on progress towards meeting the goals for improvement. Any barriers will be discussed and further resources and supports provided as needed. A particular focus in this visit will be on ensuring that preventive care is available for all patients including disadvantaged patients who may have low health literacy.

Practice visit three occurs between three and four weeks after visit number two. The purpose of this visit is to monitor improvements, workshop ways to overcome barriers and discuss how improvements might be maintained and incorporated as part of routine practice.

The Intervention Facilitator will conduct three follow-up and troubleshooting phone calls with the prevention coordinator. Each of the practice visits will be interspersed by a follow-up or trouble shooting phone call initiated by the intervention facilitator. Additional contact may be initiated by the prevention coordinator as required.

#### Participants and recruitment

Eight practices have been recruited by a primary care organisation (Medicare Local) in each of the four states (a total of 32 practices). Staff members from the Medicare Locals approached practices that met the eligibility criteria, such as having computerised medical records to enable an audit of medical records using the Pen Clinical Audit Tool (Pen CAT)
[27] and a PN. Of the 47 practices who expressed interest in the study and who were subsequently visited, 32 agreed to participate, a response rate of 68%. Figure
2 shows the selection and randomisation process.

In each practice, participants include practice staff and patients. As a minimum, at least one GP, one PN and one practice manager from each practice is involved in the study. However, in some of the group practices, two or more GPs are involved in the research. Of the 32 practices involved in the research, only seven are in solo practices whereas 15 of the practices employ five or more GPs and ten of the practices employ between two and four GPs (Figure
4).

**Figure 4 F4:**
[figure not shown]
Participant Flow Diagram for the PEP Study consistent with the Consolidated Standards of Reporting Trials (CONSORT) 2010 statement.

The patients of the practice will be involved in the study in two ways. Firstly the records of all patients aged between 40 to 69 years who are active patients of the GPs who agree to participate in the study, and without known cardiac disease, stroke, or diabetes will be extracted in a de-identified audit at baseline and 12 months. In order to be seen as an active patient for the purpose of this study, patients must have visited their GP within the practice at least once in the last 12 months. Secondly, a random sample of 160 patients from each practice who consent and meet the eligibility criteria will be invited to complete the patient survey. To be eligible to participate in the study patients must have sufficient English and cognitive ability to understand the patient information letter, consent form, and written questionnaire.

#### Data collection procedures

Data will be collected from the practices, the practitioners and the patients for all 32 practices involved in the study (Figure
5). Data will be collected from practices by field research staff not involved in the conduct of the intervention. However, it may not be possible to fully blind them to allocation because practice staff may incidentally inform them during their visits.

**Figure 5 F5:**
[figure not shown]
Step by step description of the PEP study.

The practice manager or the principal GP from each practice will be asked to complete a Practice Assessment Survey that collects descriptive information about the practice, including the location of the practice, number, type, and roles of staff members and information systems used. This information will assist us in understanding how the practice operates and therefore in identifying opportunities to facilitate preventive care. During the analysis phase of the research, the collation of practice information will enable us to examine whether any patterns of preventive care improvements emerge according to practice location, size, and teamwork arrangements.

Information will then be collected from the practitioners at baseline and again at 12 months. The GPs and PNs are asked to complete a survey that asks about their demographic characteristics and years in practice, and also how preventive care assessment and management is provided including frequency of assessment and management of the behavioural and physiological risk factors. This survey is based on questions from the Preventive Medicine Attitudes and Activities Questionnaire (PMAAQ)
[28] used by us in previous research
[29].

Patient information is also collected at baseline and again at 12 months to enable us to identify changes in the level of risk for CVD (Table
1). The medical record audit is conducted by the field research staff using the Pen CAT tool
[27] The data extracted includes de-identified information on the recording and level of lifestyle and physiological risk factors, and the management of hypertension, dyslipidemia, diabetes, and CVD risk assessment. The patient survey is based on the NSW Health Survey
[30] and previous research
[31]. The survey includes questions about practice attendance, reported assessment and management of behavioural risk factors—smoking, nutrition, alcohol, physical activity and weight (SNAPW)—in general practice
[7], attendances at other services as a result of referral from the practice or self-referral, self-reported fruit and vegetable intake
[32], smoking, physical activity
[33] and alcohol intake
[34], and readiness for behaviour change (stage of change) for each SNAPW risk factor
[35].

**Table 1 T1:** Outcome Variables

**Category**	**Measures**	**Time Point**
Primary		
Recorded risk factors	Proportion of eligible patients with the following recorded	0 and 12 months
	· In the previous 24 months:-	
	o Blood pressure (in patients without hypertension)	
	o Weight (with height for BMI)	
	o Waist circumference	
	o Fasting blood glucose	
	oFasting Lipids	
	· Ever:-	
	o Smoking status	
	o Alcohol intake	
Recalled Advice	Proportion of eligible patients who were at risk who recalled being offered advice:	0 and 12 months
	· Diet (fruit and vegetables, low saturated fat)	
	· Physical activity	
	· Weight control	
Medication	Change in medications over previous 12 months	0 and 12 months
	· lipid lowering,	
	· antihypertensive	
Risk factors	Self assessed:	0 and 12 months
	· Physical activity score*	
	· Diet score**	
	· Smoking Status	
	· Alcohol intake (standard drinks per week)	
	Measured	
	· BMI	
	· waist circumference	
	· blood pressure	
	· lipids (TC, LDL-C, HDL-C, TG).	
Secondary		
GP or nurse preventive care	· Self reported assessment	0 and 12 months
	· Self reported advice	
GP or nurse	· attitudes to preventive care in general practice	0 and 12 months

***** Physical activity level which combines assessment of duration of vigorous and moderate physical activity (scored 0-8, <4 considered at risk)
[36].

****** Serves of fruit and vegetables per day.

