#### Study size

The trial is being conducted in 32 practices. We estimate that the number of GPs and PNs recruited to the study will be 80.

We estimate that the records of at least 500 patients will be audited in each practice (i.e., 8,000 total). Assuming a design effect due to clustering of 1.8 based on previous studies
[45], a sample of 188 patients in each group would have sufficient power (β = 0.8 and α = 0.05) to detect a 20% difference in the proportion of patients whose lifestyle and physiological risk factors are recorded. A sample size of 500 would have sufficient power to detect an effect size if 0.3 in recorded BMI (based on ICC = 0.047), LDL-Cholesterol (ICC 0.059), and systolic blood pressure after adjusting for clustering (ICC 0.062)
[29,46,47].

It is estimated that at least 40 patients will be recruited to participate in the patient survey per practice or 640 patients in each arm of the trial. Allowing for 10% loss to follow up at 12 months, this will leave 36 patients per practice (576 in each group). Assuming a design effect due to clustering of two based on previous studies, a sample of 500 patients in each group would have sufficient power (β = 0.8 and α = 0.05) to detect a 15% difference in the proportion of patients offered education for diet or physical activity after adjusting for clustering (ICCs 0.051 and 0.035) and a 10% difference referral (ICCs 0.026 and 0.011). This sample size would have sufficient power to detect an effect size of 0.3 in serves of fruit and vegetables consumed (ICC 0.001) and physical activity scores (ICC 0.018)
[33].

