#### Statistical methods

We will examine the change of study variables within the intervention and control practices before and after interventions and compare the difference of outcomes between the two groups after adjusting for baseline differences. Primary analyses will be by intention to treat (patients and practices will be analysed as randomised, rather than by intervention actually received). We will analyse patient variables (risk behaviour, health service use, blood pressure, total cholesterol, HDL, LDL, General Practice Assessment Survey (GPAS) for within and between group differences using multilevel regression techniques adjusted for clustering of patients (level one) within practices (level two). The pre-randomisation value of each outcome will be used as lag covariates. Interactions as well as main effects will be tested. Secondary analysis will compare patients who were referred against those who were not, and defined as at risk. For cases lost to follow up at 12 months, we will conduct sensitivity analyses of the primary and secondary outcomes to determine the effect of their inclusion assuming no change in the outcome variables.

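### The BMI, waist, blood pressure and lipid level outcomes compare patients selected by routine recording, which the intervention is meant to change; the baseline covariate reduces this bias but does not remove it

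*Protocol article*

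**What the plan says.** All references are to the Protocol article.

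- **Outcomes.** Table 1 lists as primary both the proportion of eligible patients with blood pressure, weight (for BMI), waist and lipids recorded in the previous 24 months, and the measured levels of those variables. The 24-month window is attached to the recording items. No window is given for the levels.
- **Source of levels.** Under Data collection procedures, "The medical record audit is conducted by the field research staff using the Pen CAT tool" and "The data extracted includes de-identified information on the recording and level of lifestyle and physiological risk factors". The patient survey is self-report. No study measurement visit is described, and Study size speaks of "sufficient power to detect an effect size if 0.3 in recorded BMI".
- **Intended effect on recording.** The Background hypothesises an improvement "by 20% recording of behavioural and physiological risk factors". Description of intervention names better recording as a possible practice goal.
- **Level hypothesis.** The Background hypothesises a 5% improvement in risk factors, limited to patients who have them.
- **Analysis.** Statistical methods specifies intention to treat and multilevel regression, and states that "The pre-randomisation value of each outcome will be used as lag covariates". A sensitivity analysis assumes no change for cases lost to follow-up.

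**The concern.** A level exists only where the practice entered one. If the intervention works as intended on recording, more intervention patients than control patients will have a 12-month value. If the chance of being recorded also depends on the patient's level, the two sets of recorded patients differ even when no patient's risk has changed. Analysing practices and patients as randomised does not protect against this, because selection happens after randomisation.

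The two stated safeguards do not fully cover it:

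- The baseline covariate can be used only for patients recorded at both audits, and re-recording is itself open to the intervention.
- The no-change rule is for cases lost to follow-up. A patient who still attends but has no new value is not obviously such a case, and a newly recorded patient has no baseline value to carry forward.

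A difference in BMI, blood pressure or lipids could therefore be created or hidden by a change in who is measured. These are the trial's measured patient-level outcomes.

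**Working it through.** **The plan's own figure.** Study size gives 500 for an effect size of 0.3, with ICCs of 0.047 (BMI), 0.059 (LDL cholesterol) and 0.062 (systolic pressure). I read 500 as per group, over 16 practices.

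- Unclustered: n = 2(1.96 + 0.84)²/0.3² ≈ 175 per arm.
- Patients per practice: m = 500/16 = 31.25. Design effect = 1 + 30.25 × ICC.
- Results: 175 × 2.42 = 424; 175 × 2.78 = 487; 175 × 2.88 = 503.

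The stated 500 is reproduced at the largest ICC, so 0.3 SD is a fair yardstick.

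**Assumptions, none of them in the document.** No true effect on level. Recording 50% in control and 70% in intervention at 12 months, reading 20% as absolute. Correlation 0.8 between a patient's values at the two audits. Recording is logistic in the current value, with log-odds 0.2, 0.4 or 0.6 per SD, so higher-risk patients are recorded more often.

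**Simulated difference, intervention minus control (SD)**

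| Log-odds per SD | Unadjusted, all recorded at 12 months | Baseline covariate, recorded at both audits |
|---|---|---|
| 0.2 | −0.040 | −0.016 |
| 0.4 | −0.077 | −0.028 |
| 0.6 | −0.111 | −0.040 |

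Repeat runs moved the last column by only a few thousandths (largest −0.041). As a share of the target, 0.015/0.3 = 5% and 0.041/0.3 = 14%. If recording favoured lower-risk patients, the signs would reverse.

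**Cross-checks on the unadjusted column.**

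- If newly recorded patients are 0.2–0.4 SD healthier than those already recorded, the shift is (0.20/0.70) × 0.2–0.4 = 0.06–0.11 SD.
- A latent-normal selection model (correlation of recording with level 0.1–0.5, control recording 40–60%) gives −0.03 to −0.16 SD for a 20-point rise.
- With 20% read as relative (control recording 30–70%), the same model gives −0.01 to −0.10 SD.

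**Scale against sampling error.** With 16 × 500 audited records per arm, the variance of an unadjusted difference is the sum over p = 0.5 and 0.7 of [1 + (500p − 1) × ICC]/(8,000p). At ICC 0.047 this is 12.70/4,000 + 17.40/5,600 = 0.00628, a standard error of 0.08 SD; at ICC 0.062 it is 0.09 SD. The covariate-adjusted bias is thus up to about half of that standard error (0.041/0.08). More records per practice would not shrink the bias.

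**Old values counted as 12-month values.** A 24-month look-back at the 12-month audit reaches 12 months before baseline. If it governed levels, a patient not re-measured would contribute the same value twice. Take an at-risk group whose baseline mean is M SD above the population mean, and for simplicity let re-recording be unrelated to level. The true mean at 12 months is 0.8M, while an old value still shows M. Old values make up 50% in control and 30% in intervention, so the spurious difference is (0.50 − 0.30) × (1 − 0.8) × M = 0.04M. For M = 1.0, 1.25 and 1.5 this is 0.04, 0.05 and 0.06 SD, favouring the arm with more re-measurement. In an unrestricted group M is near zero and so is the artefact. With recording dependent on level as above, simulation in a baseline at-risk set gave −0.050 to −0.055 SD with old values counted and −0.016 to −0.037 SD with post-randomisation values only.

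**Would imputation or weighting on baseline data help?** Under the same set-up, imputation from baseline left −0.015 to −0.042 SD and inverse-probability weighting on baseline left −0.016 to −0.040 SD. Neither improves on the covariate analysis, because recording depends on the current value even after baseline is known.

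**The case against.** The strongest reply is that the plan adjusts for the baseline value. A reader might infer that newly recorded patients enter the comparison and that the bias is therefore 0.06–0.11 SD, up to 38% of the target. The document does not support that: newly recorded patients have no baseline value, so on the natural reading of the stated model they drop out. The larger figures describe an unadjusted comparison that the article does not state. This part of the objection stands, and the size to use is the smaller one.

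Four further points stand in part.

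- A reader might infer that success on recording necessarily corrupts the level comparison. It does so only if recording depends on level, and the document gives neither that relation nor its direction.
- A reader might infer that the plan admits old values as 12-month levels. It gives no window for levels, so this is a conditional risk; a fuller plan may settle it.
- Missing-data methods commonly sit in an analysis plan, and their absence from an article is no fault. What the article does fix is the outcome and its source, and those create the problem.
- That levels come only from routine records is an inference from the one source described and the reference to recorded BMI. The figure setting out the study steps is not shown, but no text points to direct measurement.

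The recording outcomes are not affected, since their denominator is all eligible patients.

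**Conclusion.** The concern holds as a structural weakness of moderate size. The level outcomes are compared on patients selected after randomisation by a process the intervention is designed to change, and neither the intention-to-treat statement, the baseline covariate nor the no-change rule removes this. Under the assumptions listed, the residual bias in the covariate-adjusted analysis is about 0.015–0.04 SD (5–14% of 0.3 SD), in either direction. Counting old values in an at-risk group would bring the total to about 0.05 SD (0.05/0.3 = 17%), in favour of the arm with more re-measurement. These sizes rest on assumed recording rates, correlation and selection strength. The existence of the problem needs only that the intervention changes recording and that recording depends on level.

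A reader might also conclude that these measures cannot remain primary. That does not follow: moving them to secondary is a design preference.

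**What to change.** For the measured levels (BMI, waist, blood pressure, lipids), specify the following before the 12-month audit is analysed:

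1. Define the analysis set, and the at-risk set, in both arms from values present in the baseline audit.
2. Count a 12-month value only if it is dated after randomisation.
3. Report recording and re-recording rates by arm beside each level result. Add a delta-adjusted (not-at-random) sensitivity analysis for patients recorded at baseline but not re-recorded, letting delta differ by arm and sign. Interpret level differences only in that light.

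Imputation or weighting on baseline data may be added but should not be presented as removing the bias. Demotion to secondary is optional.

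**Cost.** Analysis wording and some programming. There will be fewer analysable patients and slightly wider intervals, and the level result will apply to patients already recorded at baseline. The fix needs recording dates, which the 24-month recording window suggests are available although the article does not say so. It also needs individuals linked across the two de-identified extracts, which a patient-level baseline covariate already requires. Trial status reports baseline collection complete and the intervention begun, so the rules can still be set ahead of the 12-month data.
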